### Statistical analysis

The results of the enteral and parenteral group will be compared with results of the control group. Differences between the (par)enteral and control group will be analyzed with Chi-square tests for categorical variables, with unpaired t-tests for continuous variables, and with the Mann-Whitney U test for non-normally distributed data. Correlations will be analyzed with Pearson's correlation or with the Spearman rank correlation coefficient. Multiple linear and multiple logistic regression models will be used to determine if differences between groups can be explained by the effect of (par)enteral nutrition, by confounders or by both. A p-value of ≤ 0.05 will be considered statistically significant.

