### Blood and tissue samples

Blood sampling will be done at baseline (approximately two weeks before CABG during a visit at the hospital outpatient clinic), at the day of surgery (once before and twice during surgery), at the first and third day after surgery, and approximately three weeks after surgery (during a visit at the hospital outpatient clinic) (Table 2).

During surgery, two tissue samples of the appendix of the right atrium will be taken by the surgeon. One sample will be taken prior to the start of the anastomosic connection of the bypass graft, and one sample at the end of the procedure before closing of the pericardium. Half of each sample is placed in an aluminum box which will be immediately frozen in liquid nitrogen and stored at -80°C until the amino acid profile is analyzed. The other half of each sample is immediately placed in formalin and will be analyzed within two weeks for the assessment of cardiomyocytes structure. In addition, a sample of aortic tissue is taken by the surgeon at the end of the CABG-procedure which becomes available due to fixation of the proximal anastomosis needed for the bypass and is in routine clinical practice discarded. The sample is immediately frozen in liquid nitrogen and stored at -80°C until the ADMA concentration is measured.

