### Nuclear medicine imaging techniques

An ECG-gated MPS and a ^18^F-FDG PET scan are performed at baseline (approximately two weeks before CABG) and more than three weeks after CABG. Stress and rest myocardial perfusion scintigraphy (with single-photon emission computed tomography (SPECT)) is performed with ^99 m^Tc labeled Tetrofosmin. Symptom limited exercise is the preferred stress modality. Pharmacological vasodilatory stress with adenosine will be applied if there is an insufficient increase of heart rate (<85% age predicted maximal heart-rate) during physical exercise, in the presence of a left bundle branch block, or if the anti-anginal medication had not been adequately discontinued. Dobutamine stress testing is performed in patients with a contra-indication for adenosine. The type of stress test applied for MPS before surgery is maintained at the MPS post-surgery. ECG-gated image acquisition is performed for the assessment of parameters of left ventricular function (end-systolic and end-diastolic volumes and ejection fraction). Two experienced nuclear medicine physicians analyze the images in a total of 17 myocardial segments. Segments are scored with a 5-point scoring system (0 = normal; 1 = equivocal; 2 = moderate reduction; 3 = severe reduction; 4 = absent activity). Summed stress score (SSS) and summed rest score (SRS) are obtained by adding the scores of all segments of respectively stress and rest images. The summed difference score (SDS) is calculated by subtracting the SRS from the SSS. Reversible myocardial perfusion defects, indicative for inducible myocardial ischemia, are defined as SDS ≥3. Fixed defects, indicative for scarring are defined as a SRS-score of ≥3. The presence of either reversible or fixed defects is defined as the presence of any perfusion defect.

^18^F-FDG is a glucose analogue that after cellular uptake via the GLUT-4 transporter and phosphorylation by hexokinase is not further metabolized. Therefore the imaged concentration of ^18^F-FDG in the heart reflects its glucose metabolism. Patients are imaged after suppression of the free fatty acid metabolism by oral administration of acipimox. The glucose metabolism in the myocardium is analyzed by standardized uptake values, both regional as for the total myocardium.

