### Bioelectrical impedance spectrometry

A BIS-measurement (BodyScout, Fresenius Kabi, 's-Hertogenbosch, The Netherlands) is performed at baseline and approximately three weeks after CABG for the assessment of body composition. The principle of the BIS is based on the conductance through body fluid of an electric current (5-800 μA, 5 kHz-1 MHz). The BIS measures the impedance at a range of frequencies from which the resistances of extra-cellular water and intracellular water are extrapolated. Resistance is measured on the right side while patients in supine position. Subsequently, FFM is calculated (FFM is linearly related to height^2^/body resistance) [11].

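### The stated tests give the day -14 values no defined role; baseline-adjusted ANCOVA should be the main analysis for continuous outcomes that have one

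*Protocol article*

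**What the plan says.** The Statistical analysis section compares the nutrition arms with control for continuous data "with unpaired t-tests for continuous variables, and with the Mann-Whitney U test for non-normally distributed data". It then adds a second layer: "Multiple linear and multiple logistic regression models will be used to determine if differences between groups can be explained" by nutrition, "by confounders or by both". No covariate is named, and the outcome's own baseline value is not mentioned. The significance rule is "A p-value of ≤ 0.05 will be considered statistically significant".

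Elsewhere the article collects a pre-treatment value for many outcomes:

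- Plasma: "Blood sampling will be done at baseline (approximately two weeks before CABG during a visit at the hospital outpatient clinic", and again around surgery and at the later clinic visit.
- Perfusion scintigraphy and FDG PET: these "are performed at baseline (approximately two weeks before CABG) and more than three weeks after CABG".
- Bioelectrical impedance, giving fat free mass: it "is performed at baseline and approximately three weeks after CABG for the assessment of body composition".

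Table 2 places these baselines at day -14, before the first nutrient drink at day -7. The second and third aims (Background) are framed as effects before and after surgery, and the Abstract says that changes in the imaging outcomes are evaluated. Cardiac tissue is taken only during surgery (Blood and tissue samples), so it has no pre-treatment value.

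**The concern.** The test for the group comparison is fixed in the text, and it is an unadjusted two-sample test. How the baseline enters that test is left open. If follow-up values are compared, stable differences between patients stay in the error term. If changes are compared, the full baseline value is subtracted, which adds noise when baseline and follow-up are only weakly related. With 16 patients per arm, either loss can matter.

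The role given to regression does not settle this. In a randomised comparison any baseline imbalance is due to chance. The reason to adjust is precision, using covariates named in advance. Asking whether a difference is explained by confounders, with none named, leaves an unadjusted and an adjusted answer for each outcome and no rule for which one counts.

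**Working it through.** The article states no power, SD, effect size or baseline to follow-up correlation, so it has no figure of its own to reproduce.

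**Inputs from the article:** 16 per arm (Setting); significance level 0.05 (Statistical analysis).

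**Assumed:** two-sided testing; each nutrition arm compared separately with control; a true difference of 0.8 SD; the same SD at baseline and follow-up; correlation r between baseline and follow-up of 0.3, 0.5, 0.7 or 0.8.

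**Step 1, t-test on follow-up values.** The standard error is SD × √(1/16 + 1/16) = 0.3536 SD. The noncentrality is 0.8 / 0.3536 = 2.263, with 30 df and critical value 2.042. Power is 59.1% at every r.

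**Step 2, t-test on changes.** The variance relative to step 1 is 2(1 − r), so the noncentrality is 2.263 / √(2(1 − r)), with 30 df.

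**Step 3, ANCOVA.** The relative variance is (1 − r²), multiplied by 1 + 1/28 for estimating the slope in 32 patients. The noncentrality is 2.263 / √((1 − r²)(1 + 1/28)), with 29 df and critical value 2.045.

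| r | Follow-up t-test | Change: relative variance, noncentrality, power | ANCOVA: 1 − r², noncentrality, power |
|---|---|---|---|
| 0.3 | 59.1% | 1.40, 1.912, 45.7% | 0.91, 2.331, 61.5% |
| 0.5 | 59.1% | 1.00, 2.263, 59.1% | 0.75, 2.567, 69.9% |
| 0.7 | 59.1% | 0.60, 2.921, 80.7% | 0.51, 3.113, 85.3% |
| 0.8 | 59.1% | 0.40, 3.578, 93.3% | 0.36, 3.706, 94.7% |

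**Step 4, gain from ANCOVA, in percentage points of power.**

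- Over the follow-up t-test: about 2, 11, 26 and 36 at r = 0.3, 0.5, 0.7 and 0.8.
- Over the change-score t-test: about 16, 11, 5 and 1.
- At r = 0, ANCOVA has 57.5% against 59.1% for the follow-up t-test, a cost of about 2 points.

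**Step 5, the same in patients.** Ignoring the small finite-sample factor, a follow-up t-test needs 16 / (1 − r²) per arm to match ANCOVA with 16. That is 17.6, 21.3, 31.4 and 44.4 at the four correlations.

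**Check by simulation.** At a larger effect (1.02 SD, where the follow-up t-test has 80% power), 20,000 simulated trials per setting agreed with these formulas to within about one point. All three tests kept a type I error close to 5%.

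**If the nutrition arms are pooled (32 versus 16),** which the wording could also mean, the pattern is the same. The difference detectable with 80% power is 0.88 SD for the follow-up t-test. With ANCOVA it is 0.77 SD at r = 0.5 and 0.63 SD at r = 0.7.

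**The case against.** The strongest reply is that the article never says the baseline is ignored. A reader might infer that from the bare list of tests, but the Abstract speaks of changes and two of the aims are framed as before and after surgery. An unpaired t-test on changes fits all of this and does use the baseline. For outcomes that are stable within a patient, where r is high, it gives up little: about 5 points at r = 0.7 and 1 point at r = 0.8. This stands, and it is why the point cannot be put as the plan discarding its baseline data.

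A reader might also infer that much of the available precision is lost. The documents do not support that as a general statement, because they give no correlation, SD or expected effect. At r = 0.3 or below, ANCOVA adds at most about 2 points over a follow-up t-test. A claim that the unadjusted results would be mostly noise has no source here either.

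Third, regression is announced in advance and could include the baseline value, so calling it an after-the-fact check would be conjecture. Covariate lists are commonly left to an analysis plan, and their absence from an article is no fault. What remains is what the article does state: the group comparison is an unadjusted test, and regression has an explanatory purpose rather than being the main estimate.

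Last, the scope is limited. Tissue amino acids, enzyme activity and cardiomyocyte structure make up a large part of the main outcomes and have no baseline. Among the main outcomes, only the plasma measures are affected.

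**Conclusion.** The point holds in a limited form. For continuous outcomes with a day -14 value, the article fixes a valid but generally less efficient test and does not say which quantity is tested. ANCOVA is close to or better than the better of the two t-tests at every assumed correlation, and at worst costs about 2 points of power when r is near 0. A choice between follow-up values and changes made without knowing r can cost up to 36 points one way (follow-up values at r = 0.8) or 16 the other (changes at r = 0.3), over the range shown. These sizes rest on an assumed 0.8 SD effect, equal SDs at both times, two-sided testing, full data on 16 per arm and roughly normal outcomes. This is a matter of efficiency and clarity, not of bias or an invalid test, and the change is worth making because the data are already being collected.

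**What to change.** For every continuous outcome with a day -14 value (plasma amino acids, ADMA, SDMA and the arginine/ADMA ratio, perfusion scores, ventricular volumes and ejection fraction, FDG uptake, fat free mass), name ANCOVA as the main between-group analysis. The model is the follow-up value on randomised group, with the patient's own baseline value as covariate, and with skewed concentrations and ratios log-transformed. For the plasma main outcomes, the follow-up value is the one at surgery. State that this model gives the reported answer, and name any further covariates before unblinding. Drop the aim of sorting differences into nutrition and confounding.

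Keep unadjusted tests for tissue and cardiomyocyte-structure outcomes, which have no pre-treatment value.

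The cost is a change of wording and one degree of freedom per model. No further measurement or patient is needed. The downside is the loss of about 2 points of power for any outcome whose baseline turns out to be nearly unrelated to follow-up.

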### Participants

Patients undergoing cardiac bypass surgery are selected to study the effects of (par)enteral nutrition on human cardiac tissue. In order to prevent cardioplegic effects on cardiomyocytes, selected patients are undergoing an off-pump CABG-procedure. Forty-eight patients with stable anginal complaints planned for an elective CABG who meet all inclusion criteria and do not have any of the exclusion criteria (Table 1) will be randomized by computer-generated block randomization (each block including six patients) to one of the three study groups.

**Table 1 T1:** Inclusion & exclusion criteria

Inclusion criteria:	
	•Undergoing off-pump CABG-surgery
	•Age 18 till 80 years
Exclusion criteria:	
	•Combined valve and CABG procedure
	•Age <18 and ≥ 80 years
	•Diabetes mellitus type I
	•Pregnancy
	•Renal insufficiency defined as creatinine > 95 μmol/L for women and > 110 μmol/L for men
	•Liver insufficiency defined as ALAT > 34 U/I for women and > 45 U/I for men

ALAT, alanine aminotransferase; CABG, coronary artery bypass grafting;.

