### Setting

Figure 1 depicts a flow chart of the study protocol. The study is currently performed at the department of cardio-thoracic surgery of the AMC. Patients are informed about the study by a cardiologist and nutritionist who hand over the information letter as well as the informed consent form. A patient is included in the study when the informed consent form is signed. Subsequently, the patient can be randomized to one of the three groups: the "enteral group" (n = 16), the "parenteral group" (n = 16), or the control group (n = 16). During visits at the hospital outpatient clinic (approximately two weeks before surgery), patients are subjected to baseline measurements including blood sampling, measurement of body weight and height, bioelectrical impedance spectrometry (BIS), ECG-gated myocardial perfusion scintigraphy (MPS) and a ^18^F-fluorodeoxy-glucose positron emission tomography (^18^F-FDG PET) scan (Table 2). As part of the preoperative evaluation, patients will also undergo preoperative assessments by a cardiothoracic surgeon and an anesthesiologist.

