### Outcome measures

The main study outcomes are amino acid profile and cardiomyocytes structure at the time of cardiac surgery. Amino acid profile will be studied in blood plasma and cardiac tissue and includes determining the concentrations of all amino acids, ADMA and symmetric dimethylarginine (SDMA, ADMA's isomer that lacks direct NOS inhibitory activity). In addition, the arginine/ADMA ratio (an indicator of potential NO production) will be calculated. In cardiac tissue, also the activity of dimethylarginine dimethylaminohydrolase (DDAH, an enzyme which degrades ADMA) and arginase (an enzyme which metabolizes arginine) are measured. Cardiomyocytes structure will be assessed by histological analysis, immuno-histochemistry, and by electron microscopy.

The secondary study outcomes are cardiac perfusion, left ventricular function and cardiac glucose metabolism. ECG-gated MPS will be used for the measurement of cardiac perfusion and left ventricular function. Cardiac glucose metabolism will be measured with ^18^F-FDG PET.

BIS measured FFM will be used as parameter of nutritional status. A high FFM is related to better nutritional status and improved post-surgical outcome [9]. Other outcome parameters are cardiac muscle damage and signs of failure as measured by blood plasma biomarkers (Troponin T, CK-MB, and NT-proBNP). Blood plasma will be stored for future study of metabolic switch biomarkers. Baseline characteristics (including European System for Cardiac Operation Risk Evaluation score (EuroSCORE) [10], and unintended weight loss) will be recorded, as well as clinical parameters (intensive care unit (ICU) stay, length of hospital stay, time of mechanical ventilation, organ failure, infections, bleeding, and postoperative mortality). Finally, the concentration of ADMA will be measured in a sample of the aortic wall to investigate the relation between tissue ADMA concentrations in the aorta, and both intracellular concentrations from peripheral blood mononuclear cells (PBMC) and plasma levels.

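### With 16 patients per arm, ordinary multiple logistic regression will often give no finite group odds ratio for any binary outcome that occurs in about 10% of patients or fewer

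*Protocol article*

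**What the plan says.** The Participants and Setting sections give 48 patients, 16 in each of the enteral, parenteral and control groups, "randomized by computer-generated block randomization (each block including six patients) to one of the three study groups".

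The Statistical analysis section states the contrasts: "The results of the enteral and parenteral group will be compared with results of the control group". Unadjusted group differences "will be analyzed with Chi-square tests for categorical variables". For the adjusted analysis, "Multiple linear and multiple logistic regression models will be used to determine if differences between groups can be explained" by nutrition, by confounders or by both. The section does not name or count the confounders. It does not say whether the model has one or two group terms, and it ties the logistic model to no particular outcome.

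Several recorded variables are binary and so fall under that wording. The Outcome measures section lists, among the clinical parameters, "time of mechanical ventilation, organ failure, infections, bleeding, and postoperative mortality"; all but the ventilation time are yes/no events. Baseline and Clinical characteristics defines them. Organ failure combines cardiac, renal and neurologic criteria, and infection covers six categories. Bleeding is limited to abdominal bleeding or reoperation for bleeding. Deaths are counted from admission to the postoperative outpatient visit. Perfusion defect present or absent (Nuclear medicine imaging techniques) is also binary, as is the presence of iron or amyloid (Tissue pathological evaluation). No expected rate is given for any of these.

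**The concern.** Ordinary logistic regression is fitted by maximum likelihood. If one of the groups compared has no event, or only events, the likelihood keeps rising as the group coefficient grows. The odds ratio is then zero, infinite or undefined, and its usual Wald interval has no meaning. This is separation. Each added covariate opens further ways for it to happen, because a combination of group and covariates may sort events from non-events.

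With 16 patients per arm, an empty cell is a real prospect for a rare outcome. The logistic model is also the article's stated tool for separating the nutrition effect from confounding. If it fails, the analysts must either replace it after seeing the data or publish an odds ratio that carries no usable information. Because the method is fixed in the text, this is a question of whether it suits the fixed sample size, and not of detail left for an analysis plan.

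**Working it through.** **Inputs.** Arm size 16, three arms, N = 3 × 16 = 48 (Participants, Setting). The article gives no event rate, effect size or power figure, so there is no figure of its own to reproduce on this point. Event rates *p* from 5% to 30%, equal in all arms, are assumptions.

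**Unadjusted model, one nutrition arm against control (16 v 16).** The group odds ratio is finite only if both arms contain at least one event and one non-event. For one arm this has probability

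f = 1 − (1−p)^16 − p^16,

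and the probability of no finite odds ratio is 1 − f².

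At p = 0.10: (0.90)^16 = 0.185, p^16 is negligible, f = 0.815, and 1 − 0.815² = 0.336.

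| Assumed rate | Expected events per arm | (1−p)^16 | 16 v 16, no finite odds ratio |
|---|---|---|---|
| 5% | 0.8 | 0.440 | 69% |
| 10% | 1.6 | 0.185 | 34% |
| 15% | 2.4 | 0.074 | 14% |
| 20% | 3.2 | 0.028 | 6% |
| 30% | 4.8 | 0.003 | about 1% |

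The formula is symmetric in p and 1 − p, so an outcome present in 90% of patients behaves like one present in 10%.

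**Other readings of the contrast.** If the two nutrition arms are pooled (32 v 16), the figures at 5%, 10%, 15% and 20% are 55%, 21%, 8% and 3%. In a single three-arm model, the chance that at least one arm has an empty cell is 1 − f³: 82%, 46%, 21% and 8%. The 16 v 16 contrast lies between the two.

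**Adjusted model, 16 v 16.** The number of covariates is not stated. Two were assumed, one normal and one binary with 25% prevalence, both unrelated to outcome. Simulated trials were checked for complete or quasi-complete separation by linear programming. The share with no finite maximum likelihood estimate was about 85% at a 5% rate, 58% at 10%, 37% at 15%, 20% at 20% and 10% at 30%. Repeat runs gave 84–85%, 57–59%, 36–37%, 20–23% and 8–10%, so these are good to a few percentage points.

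These shares count separation in any coefficient, including a covariate's. An empty cell in one arm always makes the group coefficient non-finite. The chance that the adjusted group odds ratio itself fails therefore lies between the unadjusted and adjusted figures, for example between 34% and about 58% at a 10% rate.

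**Chi-square test, for comparison.** Full enumeration of all 16 v 16 tables gives the true type I error of the uncorrected test at nominal 5%. It is 0.6% at a 5% event rate, 2.8% at 10%, 5.3% at 20% and 5.7% at 30%. Fisher's exact test gives 0.1%, 0.7%, 1.8% and 1.8%.

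**The case against.** **The rates are assumed.** This stands. Nothing in the article says that events are rare, and a reader should not infer that logistic regression fails for every binary outcome. Composite organ failure and all infections together may be common enough to estimate. For perfusion defects, in patients with stable angina scheduled for bypass surgery, nothing supports a rate of 5–15%. The concern is conditional. It is most plausible for death and for bleeding as narrowly defined, since patients are elective and renal insufficiency and combined valve surgery are excluded.

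**The methods are not tied to clinical events.** This also stands. They are named for categorical variables in general, and the clinical events are among several variables covered.

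**The chi-square test might seem invalid too,** because expected counts fall below 5 for any rate under 5/16 = 31%. The numbers do not support that. Its true error never exceeds 5.7% at the rates checked, and Fisher's test lies further below the nominal level at those rates.

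**The imaging cut might seem to discard information.** The article says "Reversible myocardial perfusion defects, indicative for inducible myocardial ischemia, are defined as SDS ≥3", but that only defines what is called a reversible defect. The same section derives the summed stress, rest and difference scores and does not say that only the yes/no version will be analysed. No criticism of the cut is supported.

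**Small-sample methods belong in the analysis plan.** This is partly right: a covariate list or a fallback rule may be there. But the article does name a method, and where events are rare that method, applied as written to arms of 16, often has no estimate.

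**Conclusion.** The point holds, conditionally and as a minor one. For a binary outcome at about 10% or lower (or about 90% or higher), ordinary logistic regression comparing 16 with 16 gives no finite group odds ratio in at least a third of trials unadjusted. With two covariates the model fails in more than half. By a rate of about 30% the failure largely disappears. The size rests on assumed rates equal across arms, on two assumed covariates, and on each nutrition arm being compared separately with control; pooling the nutrition arms reduces it.

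A reader might infer that the trial's main comparisons are undermined. They are not. Amino acid profile and cardiomyocyte structure consist almost wholly of measured quantities; the presence of iron or amyloid is an incidental yes/no item. Organ failure, infection, bleeding and mortality are recorded as clinical parameters in a trial that calls itself proof-of-concept, and no main conclusion depends on their odds ratios.

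**What to change.** In the Statistical analysis section, limit ordinary multiple logistic regression to binary outcomes with adequate counts. For outcomes with few events or few non-events, state one of the following:

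- Firth's penalised logistic regression, which gives finite estimates under separation, with group and at most one baseline covariate named in advance; or
- event counts per arm and the risk difference with an exact interval for each nutrition arm against control, with no adjusted model. With 0/16 against 2/16, for instance, the odds ratio is not finite, but the risk difference of 2/16 = 12.5 percentage points can still be reported with its interval.

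What counts as few should be fixed before the outcome data are seen. Applying the chosen method to every binary outcome would avoid the need for a threshold.

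The chi-square test and the definition of perfusion defects need no change on this account.

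The change is to wording only. It gives up some confounder adjustment for these exploratory outcomes, although randomisation already protects the group comparison from systematic confounding. The intervals will be wide, which reflects what 16 patients per arm can show about rare events.
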